#### Secondary outcomes

These will include our aggression/bullying measures (GBS and ESYTC) measured at 24 months and other outcomes measured at both 24 and 36 months:Student-self-report outcomes: these will be measured through student survey self-reports:Paediatric quality of life inventory (PedsQL) version 4.0 will be used to assess overall QoL. The 30-item PedsQL [63] has been shown to be a reliable and valid measure of QoL in normative adolescent populations. It consists of 30 items representing five functional domains: physical, emotional, social, school and well-being, and yields a total QoL score, two summary scores for ‘Physical Health’ and ‘Psychosocial Health’ and three subscale scores for ‘Emotional’, ‘Social’, and ‘School’ functioning.Psychological function and well-being;The Strengths and Difficulties Questionnaire (SDQ) [61] is a brief screening instrument for detecting behavioural, emotional and peer problems and pro-social strengths in children and adolescents. It is brief, quick to complete, and validated in national UK samples.Short Warwick-Edinburgh Mental Well-Being Scale (SWEMWBS) [64] is a seven-item scale designed to capture a broad concept of positive emotional well-being including psychological functioning, cognitive-evaluative dimensions and affective-emotional aspects, with a total ‘Well-Being Index’ generated.Risk behaviours;Substance use. Validated age-appropriate questions taken from national surveys and/or previous trials will be used to assess smoking (smoking in previous week; ever smoked regularly), alcohol use (use in previous week; number of times really drunk; binge drinking) and illicit drug use (last month; lifetime use).Sexual risk behaviours: age of sexual debut and use of contraception at first sex may be examined by measures used in the Ripple trial [65]. We will consult with schools about the acceptability of asking these questions at follow-up (year ten).Use of NHS services: self-report use of primary care, accident and emergency, other service in past 12 months.Contact with police will be assessed using the Young People’s Development Programme (YPDP) evaluation measure [66], which asks whether the young person has been stopped, told off, or picked up by the police in the last 12 months.

(ii) Student-level data collected from schools:School attendance will be measured via routine school data on each student expressed as number of half days absent; for which we will seek students’ informed consent to access.Educational attainment: this will be assessed by an independent team based at the University of Manchester drawing on routine data.

(iii) Individual staff-level outcomes. We will measure the following secondary outcomes through survey self-reports from teachers and teaching assistants:Staff attendance will be measured via routine school data on each staff-member expressed as number of half days absent; for which we will seek staff-members’ informed consent to access.Staff QoL will be measured using the Short Form (SF)-12 version 2 Health Survey [67], a brief well-validated measure of adult health-related QoL.Staff stress and burnout will be measured using the Maslach Burnout Inventory [68], an established scale which uses a three-dimensional description of exhaustion, cynicism, and inefficacy.

(iv) School-level outcomes: routinely-collected data on school rates of temporary and permanent exclusions.

Student surveys will be conducted in exam conditions in schools, maximizing privacy. All students in the school in that year and all teaching and teaching assistant staff will be surveyed at each time-point, not only those who participated at baseline. Paper-based questionnaires will be completed confidentially in a 45-minute class session devoted to the purpose. Field workers will supervise the class completing the questionnaire, with the teacher present (for disciplinary purposes) but unable to see the questionnaires. The field-workers will assist students with questions that they do not understand and ensure students complete as much of the questionnaire as possible. Note that students with mild learning difficulties or with limited command of written English will be supported to complete the questionnaires by fieldworkers.

We will ask students in intervention schools involved in qualitative interviews whether their reporting (as opposed to their experience) of bullying and aggression might have been affected by the intervention.

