### Research questions

RQ1. Is the INCLUSIVE intervention implemented over three school years more effective and cost-effective than standard practice in reducing bullying and aggression among 12- to 15-year olds in English secondary schools?

RQ2. Is the INCLUSIVE intervention more effective than standard practice in improving students’ quality of life (QoL), well-being, psychological function and attainments, and reducing school exclusion and truancy, substance use, sexual risk, National Health Service (NHS) use, police contacts among students, and improving staff QoL and attendance and reducing burn-out?

RQ3. What pre-hypothesised factors moderate and mediate the effectiveness of the INCLUSIVE intervention; including, do effects vary by socio-economic status and sex?

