### Study population

INCLUSIVE is a universal intervention, aimed at all 11- to 16-year olds in participating secondary schools in England. While the intervention will have effects on the whole school, our study population of students will be those at the end of year 7 (age 11 to 12 years) at baseline and at the end of year 10 at 36-month follow-up (age 14 to 15), as well as all school teaching and teaching assistant staff. All students in the school in that year and all teaching staff will be surveyed at each time-point, not only those who participated at baseline.

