### Power and sample size

The average English school has approximately 190 students per year, although this varies across schools. A systematic review of school-based secondary preventive interventions to prevent violence [69] reported a pooled effect size of 0.41 on measures of aggressive behaviour. Effect sizes for aggressive behaviour from similar interventions approximate 0.3 to 0.4 SDs in males. Recent data from three large UK school cohorts [70] suggest that intra-cluster correlation coefficients (ICC) for aggression and bullying outcomes vary between 0.01 and 0.03

We propose to recruit sufficient participants to detect a difference between groups of 0.25 SD with 90% power and a 5% level of significance. This is considered to represent a moderate size of effect and in line with the effect sizes seen in the literature.

Conservatively, taking an ICC of 0.04 and 150 students per school, a trial involving 20 schools per arm will provide 90% power to identify an effect size of 0.25 SD with a 5% significance level. If two schools per arm (that is 10%) were to be lost to follow-up over the course of the trial, we would still have 80% power to detect an effect size of 0.25 SD.

The total student sample size will be approximately 6,000. As we will be surveying all young people in the relevant school year at each follow-up, this sample is likely to remain similar across the study.

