### Analyses

#### Outcome analyses

All primary analyses will be carried out according to the principle of intention-to-treat (ITT) and using multilevel modelling to take into account clustering at the school level. The primary analysis will be a repeat cross-sectional analysis that includes data from all students at both time points for two main reasons: (1) the intervention is a whole school intervention and, based on a school-level theory of change, is expected to impact on all pupils, not just on those pupils who were present at baseline; (2) the literature suggests that in cluster randomised trials, when migration into or out of the clusters is high over time, the baseline cohort may not remain representative of the cluster and therefore repeated cross-sectional analysis is preferred to minimise bias. Based on our pilot data and existing research on student mobility, we anticipate student turn-over of up to 25% in some schools over 36 months. Because of this we will use multilevel analyses that include all students at all time-points, which essentially provides a repeat cross-sectional analysis with a nested longitudinal cohort.

Data will be analysed by appropriate multivariate regression models, fitting pre-hypothesised potential confounders as covariates. Note that data on ethnicity and socio-economic status will be collected by self-report from students. Both primary outcomes will be fully analysed and reported separately, using separate multi-level models. A small number of secondary analyses based on explicit hypotheses, for example, subgroup effects/causal pathway analyses will be specified in advance. These secondary analyses will include a longitudinal analysis of pupils present at both baseline and follow-up, with further analyses using individual-level baseline data to explore the implications of missing individual-level outcome data.

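### The only sexual-risk measures named for RQ2 exist only for students who have had sex by age 14 to 15; the 36-month outcomes should be defined over all surveyed students

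*Protocol article*

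**What the plan says.** RQ2, under Research questions, asks whether the intervention is more effective than standard practice in "reducing school exclusion and truancy, substance use, sexual risk" and other outcomes. Under Secondary outcomes, sexual risk is represented by two measures: "age of sexual debut and use of contraception at first sex may be examined by measures used in the Ripple trial". They are tentative, since the next sentence reads "We will consult with schools about the acceptability of asking these questions at follow-up (year ten").

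Study population places the cohort "at the end of year 10 at 36-month follow-up (age 14 to 15"), so year ten is the 36-month survey. The lead-in to the Secondary outcomes list, however, places the other outcomes at both 24 and 36 months.

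On analysis, the Outcome analyses section is general: "Data will be analysed by appropriate multivariate regression models, fitting pre-hypothesised potential confounders as covariates". It plans intention-to-treat analyses of all students in the year. It gives no denominator for the sexual-risk items and does not say how students who have not had sex enter the analysis. It also does not say that the analysis is restricted to those who have.

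**The concern.** Age at debut and contraception at first sex have no observed value for a student who has not had sex by the survey. Having had sex is itself a result that RQ2 hopes to change. If the arms are compared among students with a value, randomisation no longer protects the comparison: the two groups are selected by the behaviour under study.

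Two things follow. An intervention that delays debut removes some students from the intervention arm's comparison, so the remaining mean debut age understates the delay. The contraception comparison is then between different kinds of student, and an avoided debut counts for nothing.

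Other risk items in the same list, such as ever having smoked regularly, lifetime drug use and police contact in the past year, have a value for every student. Sexual risk is the exception, and the matching item (whether the student has had sex) is not named. At stake is whether the one sexual-risk result can answer that part of RQ2.

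**Working it through.** The plan states no figure for this outcome, so there is none to reproduce. The size was explored under stated assumptions.

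**Inputs from the protocol.** Survey age 14 to 15, taken as 15.0. For power: 20 schools per arm, 150 students per school and an ICC of 0.04 (Power and sample size). The ICC was given for the primary outcomes and is borrowed here.

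**Assumed inputs.** The distribution of debut age, and debut by the survey in 5% to 20% of controls.

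**Check 1: normal debut ages, everyone delayed by 0.5 years.** With z = (15 − μ)/σ, the share with debut is Φ(z), and the mean age among them is μ − σφ(z)/Φ(z).

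| μ, control to intervention | σ | Share with debut by 15 | Relative fall | Mean age among those with debut | Difference (years) |
|---|---|---|---|---|---|
| 17.0 to 17.5 | 1.5 | 9.1% to 4.8% | 48% | 14.30 to 14.38 | 0.07 |
| 16.5 to 17.0 | 1.5 | 15.9% to 9.1% | 43% | 14.21 to 14.30 | 0.09 |
| 17.0 to 17.5 | 2.0 | 15.9% to 10.6% | 33% | 13.95 to 14.04 | 0.09 |

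First row: z = −1.333, φ = 0.1640, Φ = 0.0912, so the mean is 17 − 1.5 × 0.1640/0.0912 = 14.30. A true delay of 0.5 years appears as 15% to 19% of its size.

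**Check 2: Weibull-type hazard from age 11, shape 2 or 4, control debut 5%, 10% or 20%.**

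- *Hazard ratio 0.7 or 0.5 from age 11.* Debut falls by 28% to 49%. The mean among those with debut moves 0.003 to 0.03 years, with power of 5% to 6%.
- *Same hazard ratios, acting only from age 12.* The mean moves between −0.11 and +0.01 years, so it can take the wrong sign. Power is 5% to 17%.
- *Uniform shift of 0.5 years.* The mean moves 0.10 to 0.19 years (0.16 to 0.20 SD), with power of 22% to 67%.

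Worked case: 10% control debut, hazard ratio 0.5 from age 11, shape 2.

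- *Mean among those with debut.* Control has 15 per school, design effect 1 + 14 × 0.04 = 1.56, n = 300. Intervention has 7.7 per school, design effect 1 + 6.7 × 0.04 = 1.27, n = 154. With SD 0.95, SE = 0.95 × √(1.56/300 + 1.27/154) = 0.11 years. The difference is 0.014 years, giving power of about 5%.
- *Proportion over all students.* 10.0% against 5.1%. Design effect 1 + 149 × 0.04 = 6.96, so the effective n is 3,000/6.96 = 431 per arm. SE = √[(0.100 × 0.900 + 0.051 × 0.949)/431] = 0.018. The ratio 0.049/0.018 is about 2.7, giving power of about 77%.

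With the same hazard ratio, the proportion has power of about 48% at 5% control debut and about 97% at 20%.

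The proportion is not always the more powerful summary. Under the uniform shift with shape 2 and 10% control debut, power is 21% for the proportion and 46% for the conditional mean. The case for the proportion is that it compares randomised groups, not that it wins under every model.

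**Check 3: contraception, using 10.0% and 5.1% debut.** Let u be the share of first sex without contraception among those with debut.

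- If u is the same in both arms, the conditional comparison shows no difference. Over all students, unprotected first sex is 0.100u against 0.051u, a fall of 49%.
- If the avoided debuts were all ones that would have been protected, the number of unprotected debuts is unchanged. The conditional share then rises from u to u × 10.0/5.1 = 1.96u (possible when u is at most 0.51), which looks like harm where there is none.

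**The case against.** The strongest reply is that the protocol never commits to an analysis among students with debut only. It names topics to be measured, surveys every student in the year and plans all-student analyses. An age-at-debut item also yields debut by the survey (yes/no) and time to debut censored at the survey, and either would show a delay. The items come from another trial's instrument, which is not shown and may ask directly whether the student has had sex. Coding and denominators for a tentative secondary outcome commonly sit in a full protocol or analysis plan, neither of which is shown.

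Much of this stands. A reader might infer that a delaying intervention would show almost no effect on these measures and so be reported as null. The document does not support that. It requires both a restriction to students with debut, which is nowhere stated, and a particular pattern of delay. A uniform shift leaves an attenuated but visible difference.

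What remains is which quantities are named. Contraception at first sex is undefined without debut, whatever analysis is chosen, and the article names no all-student counterpart.

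On timing, the sentence specific to these items can be read as qualifying the general lead-in. That part is a matter of wording only.

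**Conclusion.** The point holds in limited form. The two named measures are conditional on behaviour after randomisation, and no all-student measure is named for the sexual-risk part of RQ2.

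This is clearest for contraception at first sex, where the argument needs no debut distribution. For age at debut, the distortion arises only if the arms are compared among students with debut. Its size then depends on assumptions the protocol cannot settle: from near zero movement under a proportional delay, through 0.07 to 0.19 years of a true 0.5-year delay, to the wrong sign if the effect starts at age 12.

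The outcome is secondary, tentative and subject to schools' agreement, and the primary outcomes are unaffected. It is a minor improvement worth making because it costs so little.

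**What to change.** Define the 36-month sexual-risk outcomes over all surveyed students:

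1. Had sex by the survey (yes/no), or time to debut censored at the survey.
2. First sex without contraception (yes/no, with no for students who have not had sex).

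Report age of debut and contraception among students who have had sex descriptively only. State that these items are asked at 36 months (year ten) only, and reconcile this with the lead-in that places the other outcomes at both 24 and 36 months.

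The cost is a change of wording. The same questions should supply the data, provided that a student who has not had sex can say so on the questionnaire. The downside is that age of debut among those who have had sex is no longer a compared outcome.

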**Methods:**

Design: cluster randomised trial.

Participants: 40 state-supported secondary schools. Outcomes assessed among the cohort of students in year 8 (n = approximately 6,000) in intervention year 1.

Intervention: INCLUSIVE is a school-led intervention which combines changes to the school environment with the promotion of social and emotional skills and restorative practices through: the formation of a school action group involving students and staff supported by an external facilitator to review local data on needs, determine priorities, and develop and implement an action plan for revising relevant school policies/rules and other actions to improve relationships at school and reduce aggression; staff training in restorative practices; and a new social and emotional skills curriculum. The intervention will be delivered by schools supported in the first two years by educational facilitators independent of the research team, with a third locally facilitated intervention year.

Comparator: normal practice.

Outcomes: primary: 2 primary outcomes at student level assessed at baseline and at 36 months:
Aggressive behaviours in school: Edinburgh Study of Youth Transitions and Crime school misbehaviour subscale (ESYTC)Bullying and victimisation: Gatehouse Bullying Scale (GBS)

Secondary outcomes assessed at baseline, 24 and 36 months will include measures relating to the economic evaluation, psychosocial outcomes in students and staff and school-level truancy and exclusion rates.

Sample size: 20 schools per arm will provide 90% power to identify an effect size of 0.25 SD with a 5% significance level.

Randomisation: eligible consenting schools will be randomised stratified for single sex versus mixed sex schools, school-level deprivation and measures of school attainment.

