### Economic evaluation

The aim of the economic evaluation is to assess the costs, consequences and cost-effectiveness of the INCLUSIVE intervention compared with standard school-based practices for managing aggression.

The primary economic evaluation will take the form of a within-trial cost-consequence analysis, with a secondary analysis that will report relative cost-utility with health outcomes expressed in terms of Quality-Adjusted Life-Years (QALYs), as recommended by the National Institute for Health and Care Excellence (NICE)’s public health methods guidance.

This NICE guidance also recommends that the base-case cost-effectiveness estimate is presented from a public sector perspective as this allows the costs and benefits of more than one central/local government body to be taken into account. This statement is particularly pertinent to INCLUSIVE as the costs of implementing it are likely to fall on the educational sector, yet there are potential cost implications for sectors such as the NHS, the police and the judiciary through reduced anti-social behaviour.

The costs to the education sector include cost of the facilitator to deliver the intervention and the cost of staff time. The facilitator costs for the delivery of the intervention will be collected using log sheets. The impact on staff time for training and delivering bullying policy will be obtained as part of the process evaluation. It is possible that the intervention might offset some of the staff time related to dealing with pupil aggression or bullying behaviour and this will be captured as part of the teacher survey. It might also impact on teacher health and we will capture this by valuing the number of days off work, which will be captured as a secondary outcome measure. The implications for NHS resource use and policing will be identified with specific questions in the student survey and valued accordingly. The time horizon will capture costs and outcomes within the trial.

Changes in health-related QoL (as expressed using QALYs) will be measured from the study participants’ (that is student’s/teacher’s) perspective.

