The *Child Health Utility* (*CHU*) *9D measure* (CHU-9D) [71] will be used to assess student’s health-related QoL as part of the economic evaluation. The CHU-9D is a validated age-appropriate measure that was explicitly developed using children’s input and has been suggested to be more appropriate and function better than other health utility measures for children and adolescents. For teachers, we will use the SF-12 for this purpose [67]. Student and teacher utility values will be collected (at baseline and at follow-up surveys at 24 and 36 months) using the CHU-9D and by converting the SF-12 questionnaires respectively.

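### NHS use and police contact are not observed in the first intervention year, although the economic horizon is the full three-year trial

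*Protocol article*

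**What the plan says.** In the protocol article, Secondary outcomes, NHS service use is "self-report use of primary care, accident and emergency, other service in past 12 months". The police item, in the same section, is a measure "which asks whether the young person has been stopped, told off, or picked up by the police in the last 12 months".

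The abstract gives the timing: "Secondary outcomes assessed at baseline, 24 and 36 months will include measures relating to the economic evaluation". Secondary outcomes agrees on follow-up, with "other outcomes measured at both 24 and 36 months". The Economic evaluation section gives the same three survey points for the utility measures: "at baseline and at follow-up surveys at 24 and 36 months".

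That section names questions in the student survey as the source of NHS and policing resource use. Facilitator costs come from log sheets, and staff time for training and delivery from the process evaluation. On the horizon it says: "The time horizon will capture costs and outcomes within the trial". The opening of Methods describes a three-year trial. Under Economic analyses, mean costs and effects come from multilevel models, net benefit is derived from them, and missing data are to be multiply imputed.

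**The concern.** The recall period, survey times, data source and horizon are all fixed in the article, and for two cost items they do not fit together. Surveys 24 months apart with 12-month recall leave a year about which nobody is asked. Baseline is at the end of school year 7 and the first intervention year is year 8, so the missing year is the first year of the intervention and one of its two externally facilitated years.

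The gap does not affect all costs alike. The sources named for intervention costs have no recall window of this kind. The Economic evaluation section argues that a public-sector perspective is especially apt here because costs fall on education while effects may fall on the NHS, police and judiciary. NHS and police use are among the effects that could offset the intervention's cost, and they are the items with the gap.

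**Working it through.** **Inputs.** Recall is 12 months for both items (Secondary outcomes). Surveys are at t = 0, 24 and 36 months (abstract; Secondary outcomes for the two follow-ups). The horizon is months 0 to 36 (Economic evaluation; opening of Methods). The article states no coverage figure to reproduce.

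**Coverage.** A survey at month t covers t − 12 to t.

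| Survey | Months covered | Within follow-up |
|---|---|---|
| 0 | −12 to 0 | 0 |
| 24 | 12 to 24 | 12 |
| 36 | 24 to 36 | 12 |

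The total is 24 of 36 months (67%). The uncovered block is months 0 to 12 (12/36 = 33%).

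**Could another source fill it?**
- The annual needs survey is listed as an intervention input. Its stated content is bullying, aggression and their determinants, and control schools receive no additional input.
- No linkage to NHS or police records is described.
- Multiple imputation cannot recover a year that is unobserved by design for every student in both arms. It would need an assumption about that year from outside the data.
- Utility scores can be interpolated between 0 and 24 months because they are states at a point in time. Use over a 12-month window cannot be filled that way without a further assumption.

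**Size if the observed reports are summed.** Let D1, D2 and D3 be the between-arm differences in NHS and police cost per student in years 1, 2 and 3. The omitted share is D1 / (D1 + D2 + D3).
- Constant difference (S, S, S): S / 3S = 1/3.
- Growing difference (S, 2S, 3S): S / 6S = 1/6.
- Extra use in year 1, then savings (−S, S, S): the true total is S and the observed total is 2S, so the saving is overstated.

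The article gives no value for S, so no amount in pounds can be stated.

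**What simple rules for year 1 would give.** The three-year total is the assumed year-1 difference plus D2 + D3.

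| Year-1 difference set to | True pattern S, S, S (total 3S) | True pattern S, 2S, 3S (total 6S) |
|---|---|---|
| 0 | 2S | 5S |
| D2 / 2 | 2.5S | 6S |
| D2 | 3S | 7S |

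Linear interpolation between the baseline and 24-month annual reports, with balanced baselines, is the D2/2 row. Under a constant difference it still falls short by 0.5S / 3S = 1/6. No single rule is right under both patterns, so a range is needed.

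**The case against.** The strongest reply is that the article does not say how the cost total is built. It does not say that the two annual reports are summed or that year 1 is given the value zero; annualising or interpolating would be equally compatible with the text. Costing an unsampled period is commonly left to an economic analysis plan, which is not shown. The horizon sentence can also be read as ruling out extrapolation beyond the trial, not as promising continuous observation of each cost item.

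Much of this stands. A reader might infer that the plan combines three full years of intervention cost with two years of offsets. The documents do not support that: no sentence says intervention costs are captured completely, external facilitation ends after two years, and no rule for year 1 is given. Nor can the understatement be put at one third without assuming a constant difference from month 0. The action group, training and policy revision have to be set up first, so a gradual effect is plausible.

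The primary economic analysis is a cost-consequence analysis, in which items can be shown separately. Net benefit belongs to the secondary cost-utility analysis.

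The reply does not remove the gap. An analysis plan could add an assumption about year 1, but not observations. The stated data collection cannot by itself support a 36-month total for these items.

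**Conclusion.** The point holds in a limited form. NHS use and police contact are observed for 24 of the 36 follow-up months, and the first intervention year is missing in both arms. This follows directly from the stated recall and survey times; a 24-month survey held a little early would shift the boundary by weeks only.

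The consequence is conditional. If the reports are summed without adjustment, the year-1 difference is lost: one third of the three-year difference under a constant effect, one sixth under linear growth, and a bias in the opposite direction if year 1 brings extra use. It would be tempting to conclude that the economic result is biased against the intervention by a known amount. The documents establish neither the direction nor the size.

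The effect falls mainly on net benefit in the secondary cost-utility analysis and on the NHS and police lines of the cost-consequence analysis. The primary outcomes are not touched.

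**What to change.** In the economic analysis:
1. State that NHS and police use is observed for months 12 to 36 only.
2. Pre-specify a year-1 estimate for the 36-month total at arm or school level. A per-student estimate would fail for joiners without a baseline report, and the article expects turnover of up to 25% in some schools.
3. Run sensitivity analyses with the year-1 difference set to zero, to half the year-2 difference, and to the full year-2 difference.
4. Report results for the observed 12 to 36 month window as well.

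This costs a few sentences and a few extra analysis runs.

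Alternatively, the 24-month survey could ask about each of the last two school years separately, which would cover 36 of 36 months. The price is a few more items, longer recall in young adolescents, and reports by joiners that pre-date their entry to the school. No extra survey wave is needed. By the article's Trial status section the baseline survey was still under way, so the 24-month questionnaire could still be changed.

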Secondary analyses will include staff outcomes and will be carried out according to the principle of ITT using the same approach to modelling as described for the student outcomes. Secondary analyses will also examine moderators and mediators. We will examine whether intervention effects are moderated by individual-level gender and socio-economic status measured using the Health Behaviours in School-aged Children (HBSC) Family Affluence Scale [74] and sex, as well as by school-level stratifying factors (single sex versus mixed sex school; school-level deprivation; value added strata); and facilitator, though these analyses may be underpowered. We will examine whether intervention effects are mediated by process and intermediate outcome measures. Other such analyses will be informed by hypotheses derived from analysis of qualitative data.

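### Student and staff attendance are defined as a raw number of half days absent in an open population, so people with less time on roll look like better attenders than they are

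*Protocol article*

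**What the plan says.** Under Secondary outcomes, item (ii), the article states: "School attendance will be measured via routine school data on each student expressed as number of half days absent". Item (iii) uses the same form for staff: "Staff attendance will be measured via routine school data on each staff-member expressed as number of half days absent". Neither item gives a number of possible half days, an adjustment for time on roll or contract fraction, or a counting period, and no other section supplies one. In the same list, exclusions are given relative to a base: "routinely-collected data on school rates of temporary and permanent exclusions".

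The population is open. Study population says: "All students in the school in that year and all teaching staff will be surveyed at each time-point, not only those who participated at baseline". Secondary outcomes repeats this and adds teaching assistants, without restricting staff to full-time contracts. Outcome analyses explains the choice of a repeat cross-sectional analysis by mobility, "we anticipate student turn-over of up to 25% in some schools over 36 months", and says "we will use multilevel analyses that include all students at all time-points". Staff outcomes are to be analysed "using the same approach to modelling as described for the student outcomes". No exposure term is named for either group.

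The Economic evaluation section plans to put a value on teachers' days off work, taken from this secondary outcome.

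**The concern.** A half day of absence can be recorded only while a student is on the school's roll, or on a half day that a staff member is contracted to work. A bare count treats everyone as having had the same opportunity to be absent. The protocol has, for good reasons, chosen a population in which that is not so.

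Research question 2 asks whether the intervention improves staff attendance and reduces truancy. Time on roll or in post accrues after randomisation, so randomisation does not guarantee that it is balanced. The same research question covers exclusion and staff burn-out, and success on either could plausibly keep people in the school longer. The better-retaining arm would then have more half days at risk and a higher mean count at the same absence rate.

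**Working it through.** The article states no attendance figure, so there is nothing to reproduce. The check compares the count with a rate.

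**Inputs from the article:** turnover of up to 25% in some schools over 36 months; everyone present at each time-point is included; 150 students per school (sample size section).

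**Assumptions not in the article:** 380 possible half days a year; a 5% absence rate (range 3% to 8%, with 300 to 380 half days); a 0.6 staff contract; leavers replaced by joiners; entry dates spread evenly over 36 months.

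**Individual values.** Expected count = absence rate × possible half days.
- Full-year student: 0.05 × 380 = 19.0. Mid-year joiner, same behaviour: 0.05 × 190 = 9.5. Over the assumed range, the pairs run from 9.0 v 4.5 to 30.4 v 15.2. The joiner's count is always half.
- Full-time staff member: 19.0. On a 0.6 contract: 0.05 × 228 = 11.4.
- Ranks can reverse. A full-year student absent 20 of 380 half days (5.3%) scores 20. One who joined about two-thirds of the way through and was absent 15 of 125 (12%) scores 15.
- As a rate, people with the same behaviour get the same value (5% in the first two examples).

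**Mean count in a school.** Joiners have on average half of the window in which they joined. Under-count = turnover × 0.5 for a 36-month window, and (turnover ÷ 3) × 0.5 for the last school year alone.
- At 25%: 0.25 × 0.5 = 12.5% over 36 months; 0.25 ÷ 3 × 0.5 = 4.2% over one year.

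**Contrast between arms, no true effect.** Ratio = (1 − under-count in the low-turnover arm) ÷ (1 − under-count in the high-turnover arm).

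| Assumed turnover | One-year window | 36-month window |
|---|---|---|
| 25% v 25% | 1.00 | 1.00 |
| 15% v 25% | 0.975 ÷ 0.958 = 1.02 | 0.925 ÷ 0.875 = 1.06 |
| 5% v 25% | 0.992 ÷ 0.958 = 1.03 | 0.975 ÷ 0.875 = 1.11 |

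**Noise with equal turnover.** Further assumptions: between-student coefficient of variation 1, between-school log-SD 0.15, and 25% turnover in every school. The relative variance of a school mean is then about 0.0228 + 1.05 ÷ 150 = 0.030 when exposure is equal. Unequal exposure adds about 2 × CV² ÷ 150, where CV is the coefficient of variation of exposure.
- One year: 8.3% joiners, CV² = 0.944 ÷ 0.958² − 1 = 0.028. The addition is 0.0004, about 1% of the variance and under 1% of the standard error.
- 36 months: 25% joiners, CV² = 0.833 ÷ 0.875² − 1 = 0.088. The addition is 0.0012, about 4% of the variance and 2% of the standard error.

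Turnover that differs between schools would add somewhat more.

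**The case against.** The strongest defence is that a number of half days is only a unit of record. A count without a counting period cannot be analysed as it stands, so the window and model may be left to an analysis plan that is not shown, and that plan could add an offset for possible half days. This stands in part: an offset would repair the analysis. But the article does not leave the metric open. It states it twice, as a count, beside an exclusion outcome stated as a rate.

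A count is also a legitimate quantity. Total days lost is what the costing needs, and that use should stay. It does not answer whether people attend better.

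The staff half has thin support. The article gives no part-time share, contract fraction or staff turnover. Contract mix before the trial is balanced in expectation by randomisation.

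A reader might infer something stronger: that false-positive rates for attendance are badly inflated. Simulated null trials with 20 schools per arm and a t-test on school means give about 16% for 15% v 25% turnover and 49% for 5% v 25%, with a 36-month count. The article does not support these as expected consequences:
- They need a 36-month window. Secondary outcomes are measured at both 24 and 36 months, so such a count would overlap the 24-month one, and the service-use and police-contact items look back 12 months. With a one-year window the error rates are about 6% and 9%.
- They need a gap of 10 to 20 points in turnover between arms, which nothing in the article suggests.
- They apply a ceiling for some schools as the average of a whole arm.

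With equal turnover the error rate stays near 5% for count and rate alike.

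**Conclusion.** The point holds as a minor one. The definition makes individual values non-comparable in a population that the protocol itself describes as mobile. The distortion per person can be large: half for a mid-window joiner, and 40% for an assumed 0.6 contract.

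The effect on the trial comparison is modest and conditional. With equal turnover and contract mix there is no bias and about 1% to 2% on the standard error. If turnover differs by arm, the bias is towards more absence in the arm that retains people better. If that were the intervention arm, the bias would hide a benefit rather than create one.

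It would be wrong to conclude that the attendance comparisons are biased as planned. That needs a difference in turnover by arm, which the article neither gives nor predicts. The primary outcomes and the sample size are untouched.

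**What to change.** In Secondary outcomes, items (ii) and (iii):
- State the counting window for the 24- and 36-month assessments.
- Define student attendance as half days absent out of possible half days on the school's roll in that window.
- Define staff attendance as half days absent out of contracted half days in that window.
- Analyse both in the planned multilevel framework, either as a count with log(possible half days) as offset or as a binomial outcome with possible half days as denominator.
- Keep the raw staff count for the costing in the Economic evaluation.

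The cost is a sentence or two in the outcome definitions and one extra field, possible or contracted half days, in the school data request already planned. Schools would have to supply that field for part-time staff too. No extra participants or survey visits are needed.
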